#### The K6 Psychological Distress Screening Questions

The K6 is a 6-item screening scale for psychological distress. It was developed, along with the K10, for the redesigned US National Health Interview Survey. The K6 demonstrates good precision in the 90th to 99th percentile range of the population distribution and consistent psychometric properties across major sociodemographic groups. The K6 has a strong ability to discriminate between the Diagnostic and Statistical Manual of Mental Disorders, Fourth Edition cases and noncases, making it suitable for use in general-purpose health surveys [33].

#### The Social Media Screening Questionnaire (Child and Caregiver Versions)

These questions are based on a series developed to systematically assess social media use and misuse in primary care and are recommended by The American Academy of Pediatrics Center of Excellence for Social Media and Youth Mental Health [34]. They extend the HEADS-4 survey, which guides the assessment of Home, Education, Activities, and Drugs in primary care. For the purposes of this study, these screening questions have been adapted to gather information from caregivers. The questions address which apps youth use, the amount of time spent online daily, whether respondents believe the youth spends too much time online, whether social media use impacts self-confidence, and whether the youth has directly experienced cyberbullying or sexual exploitation.

#### The Social Media Use Scale

The Social Media Use Scale is a questionnaire used to measure individuals’ social media use. It includes 22 items divided into 5 dimensions: social interaction, entertainment, information seeking, convenience, and social comparison [35]. The Social Media Use Scale is valid for individuals aged 12-30 years and takes 3-6 minutes to complete.

#### The Child Safety and Well-Being Survey

The Child Safety and Well-Being survey is a 9-question tool used to gather parent or legal guardian perspectives on their child’s technology use, app use, and online safety and well-being. This survey is consistently used across Aura studies on family and child digital media use.

#### Daily Mood, Stress, and Sleep Report

Daily ratings of mood, stress, sleep, and physical activity will be completed by the child. For mood, stress, and sleep, a 0-100 sliding visual analog scale with descriptive anchor points will be used, where lower ratings reflect poorer mood, higher stress, or worse sleep. For the physical activity rating, participants will choose from a 5-point scale reflecting how much activity they engaged in over the past 24 hours: none, 0-30 minutes, 30 minutes to 1 hour, 1-2 hours, and more than 2 hours. At the end of each week, the daily report will include 3 questions asking the child to reflect on mood, stress, sleep, and physical activity over the course of the week.

### Statistical Considerations

#### Specific Aims

Three specific aims will be initially addressed in this work (Textbox 1).

Specific aims.Quantify the associationDetermine the strength and direction of associations between objectively measured smartphone use (eg, total screen time, frequency of use, specific app engagement) and self-reported well-being measures (eg, Kiddie Computerized Adaptive Testing [K-CAT], World Health Organization-5 Well-being Index [WHO-5]).Differentiate engagement typesEvaluate whether distinct aspects of smartphone engagement—specifically, the types of content consumed versus overall time spent on the device—show differential associations with well-being outcomes.Identify moderating factorsInvestigate the extent to which key person-centered characteristics, including age, gender identity, and socioeconomic status, moderate the relationships observed between smartphone usage and well-being.

#### Statistical Analysis: Specific Objectives

##### Elastic Net Regression Modeling

We will employ penalized regression models to predict baseline self-report outcomes for well-being and mental health. Specifically, for each of the following outcome measures—the World Health Organization-5 Well-being Index (WHO-5) total score, the EPOCH Measure of Adolescent Well-Being total score, the K-CAT Depression Scale total score, and the UCLA Loneliness Scale total score—we will train an Elastic Net regression model using device usage features as predictors. To identify statistically significant predictors for each outcome, we will examine the coefficient estimates of the final trained model. Features with nonzero coefficients after Elastic Net regularization will be considered important predictors and explored further in post hoc analyses.

This approach will enable us to identify which specific aspects of smartphone usage are most strongly and statistically significantly associated with self-reported measures of well-being and mental health at baseline, directly addressing specific aim 1. Furthermore, by examining the patterns of significant predictors across the different outcome variables, we can gain insights into whether time- or content-based engagement metrics are differentially associated with well-being, contributing to specific aim 2. Additionally, by including potential moderators, we can begin to address specific aim 3.

The Elastic Net is a linear regression model that combines the penalties of both Lasso (L1) and Ridge (L2) methods. This approach is especially well-suited for data sets with many potentially correlated predictors, as it simultaneously performs variable selection—shrinking coefficients of irrelevant predictors to zero—and manages multicollinearity.

We consider an initial set of 21 features derived from device usage within the first 2 weeks of the study, proximate to the baseline outcome measures. Given the richness of the device usage data, there is no clear upper limit to the number of features that could be developed. However, 21 features were selected based on initial interest, divided between time-on-device metrics and content-specific engagement, in line with specific aim 2. Additional features such as age, gender identity, household income, and racial and ethnic background will be included to address specific aim 3.

Time on device features are (1) total daily screen time, (2) total daytime screen time, (3) length of screen time sessions, (4) number of problematic screen time sessions (2 or more consecutive hours), (5) length of breaks from device usage, (6) number of breaks from device usage, (7) total nighttime screen time, (8) frequency of late-night usage, (9) duration of usage (session lengths), (10) total opportunity for sleep (time offline in the sleep window), and (11) consistency in their nighttime device schedule.

Content-based features include (1) proportion of time spent on 6 categories, namely, social, social generative artificial intelligence (AI), gaming, generative AI, educational, and productivity; (2) frequency of using apps; (3) percentage of time with social AI experience for human-AI interactions; (4) number of messages sent on social platforms; and (5) ratio of consumptive versus interactive social interactions.

For each outcome variable, the Elastic Net model will be trained using 10-fold cross-validation. This robust method partitions the data into 10 equally sized folds. The model is trained on 9 folds and evaluated on the remaining fold, repeating the process 10 times so that each fold serves as the validation set once. This procedure provides a reliable estimate of the model’s generalization performance and helps mitigate overfitting. During cross-validation, we will systematically sweep across a grid of Elastic Net hyperparameters: the mixing parameter (α), which controls the balance between L1 and L2 penalties (ranging from 0 to 1), and the regularization strength (λ), which scales the overall penalty. The optimal hyperparameters will be selected based on the mean squared error performance across the 10 validation folds. After identifying these optimal values through cross-validation, the Elastic Net model will be retrained on the entire data set. The resulting model will provide coefficient estimates for each of the 21 device usage features and other moderating features (age, gender identity, etc) in predicting the respective well-being or mental health outcome. To test for moderation, these additional features and their interaction terms will be included as independent variables in the Elastic Net model during fitting. Variables with nonzero coefficients will be considered significant, and their effects on the dependent variables (scores from the WHO-5, EPOCH, K-CAT, etc) will be further investigated by comparing models with and without these moderating factors.

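### Aim 2 compares time on device with content, but the plan only inspects which Elastic Net coefficients are nonzero and never estimates that contrast

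*Protocol article*

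**What the plan says.** **The aim.** Specific Aims (Textbox 1) makes aim 2 comparative: the question is whether "the types of content consumed versus overall time spent on the device—show differential associations with well-being outcomes".

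**The analysis.** Elastic Net Regression Modeling fits one model to each of four baseline outcomes (WHO-5, EPOCH, K-CAT depression, UCLA loneliness). It says aim 2 will be informed "by examining the patterns of significant predictors across the different outcome variables". The same section gives the criterion: "Variables with nonzero coefficients will be considered significant". It also says that coefficient estimates will be examined and that features with nonzero coefficients will be explored further post hoc. The only model comparison it names is with and without the moderators, which serves aim 3.

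**The tuning.** The mixing parameter runs from 0 to 1, and the chosen values minimise 10-fold cross-validated mean squared error.

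**The features.** The time list contains "3) length of screen time sessions" and also "9) duration of usage (session lengths". It includes "1) total daily screen time, (2) total daytime screen time" and, as item 7, nighttime screen time. The content list has a social generative AI share among its six category proportions, and also "3) percentage of time with social AI experience for human-AI interactions".

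**The concern.** A differential association is a contrast between two groups of predictors. A nonzero coefficient in one group and a zero in the other does not estimate that contrast. Nor do nonzero coefficients in both groups show that both matter. A penalty tuned for prediction error routinely keeps some irrelevant predictors, so calling survivors significant attaches a word that implies error control to a rule that has none.

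Aim 2 is one of the study's three initial aims, and the article gives no other analysis for it. Followed as written, the study could report that content matters as well as time when only one of them carries signal, or the reverse.

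**Working it through.** **1. The plan's own figures.** Feature count: 11 time items, plus content 6 + 1 + 1 + 1 + 1 = 10, gives 21, as stated. Sample size: an overall R² test with 21 predictors, f² = 0.15, noncentrality f²·N, denominator df N − 22 and alpha 0.05 (assumed, not stated) gives power 0.802 at N = 160, so the article's 160 reproduces. That calculation is for the joint test of all 21 features. It does not cover a comparison of two blocks.

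**2. The pure L2 end.** If the mixing parameter is tuned to the all-L2 end (taking the stated range to include its endpoints), ridge regression sets no coefficient to zero. The result is 11 of 11 time and 10 of 10 content features significant, whatever the data. In simulation on a grid of 0, 0.1, 0.5, 0.9 and 1, this end was chosen in 46 of 200 studies (23%) with no association at N = 1000, in 68 of 200 (34%) with no association at N = 160, and in 2 of 200 (1%) with equal true effects in both blocks at N = 1000.

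**3. Signal in one time feature only.** Assumptions: R² = 0.05, all 21 features correlated 0.3, mixing above 0, minimum cross-validated error. The scenario contains no duplicated features. Ranges are across repeated runs; with 400 replicates the Monte Carlo standard error near 67% is √(0.67 × 0.33 / 400) = 0.024.

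| Result | N = 250 | N = 1000 |
|---|---|---|
| At least one content feature nonzero | 65–68% | 65–67% |
| Mean nonzero content features (of 10) | 2.0 | 1.7 |
| Mean nonzero time features (of 11) | 3.0 | 2.6 |
| Largest coefficient is the true time feature | 81% | 100% |
| Summed absolute coefficients favour time | 86% | 99% or more |

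Content survivors equalled or outnumbered time survivors in 33–38% of studies. They strictly outnumbered them in 13–18%.

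**4. No association at all.** On the full grid, some feature was nonzero in about 50% of studies at N = 1000 (mean 5.8 of 21) and in 60% at N = 160 (mean 8.1).

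**5. A block comparison for contrast.** Four items were dropped as redundant under assumed definitions (second session-length item, daytime screen time, sleep opportunity, second social-AI share). That left 8 time + 9 content = 17 columns. Each block was tested given the other:

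F = [(RSS without block − RSS full) / q] / [RSS full / (N − 18)], q = 8 or 9, alpha 0.05, 500 replicates, total R² = 0.13.

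| Rejection rate, time / content | N = 160 | N = 1000 |
|---|---|---|
| No signal | 6% / 4% | 4.8% / 2.8% |
| Time only | 90% / 5.2% | 100% / 4.8% |
| Content only | 5% / 92% | 3.8% / 100% |
| Signal split equally | 56% / 62% | 100% / 100% |

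The block test holds its error rate and separates the cases at N = 1000. At N = 160 it is short of power when the signal is split.

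**The case against.** The strongest reply is that the article nowhere counts survivors per block. It says coefficient estimates will be examined, looks for the strongest associations, and claims only insight in an exploratory study. On that reading sizes and signs will be seen. Step 3 shows that they are informative: at N = 1000 the largest content coefficient was a median 8% of the largest time coefficient (26% at N = 250). This stands, and it limits the point. More data does little for the nonzero rule but a great deal for a reading of coefficient sizes. What it does not supply is a stated comparison of sizes between blocks, or any measure of uncertainty for one.

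A reader might also infer that the feature list contains so many duplicates that the time-versus-content result is arbitrary. The documents do not support that:

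- Only the session-length repeat is explicit. Whether daytime plus nighttime equals the total, and whether the two social-AI shares coincide, depends on definitions not given and commonly left to a statistical analysis plan.
- Each suspected redundancy lies within one block, so swapping a feature for its twin moves no signal between blocks.
- With any L2 penalty, identical predictors get equal coefficients (0.429 each in a check at mixing 0.5). Only at pure lasso is the choice between them indeterminate.
- Cleaning the list is no cure. With equal true effects at N = 1000 on the full grid, time led the tally in 34% and content in 39% of studies. After removing the four items the figures were 28% and 44%. At mixing 0.5 the lead did switch (56% against 25%, then 29% against 46%), but that concerns a tally the plan does not specify.

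**Conclusion.** The point holds in a limited form. Aim 2 is comparative, yet the analysis assigned to it is inspection of nonzero coefficients. That has no error rate and estimates no difference between time and content. Under the step 3 assumptions, about two thirds of studies would label at least one irrelevant content feature significant, with little change from N = 250 to N = 1000. At the pure L2 end every feature is labelled significant. The percentages depend on the assumed correlations and effect sizes; the ridge result does not.

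It does not follow that the coefficients are meaningless, or that duplicates drive the problem. Sizes usually pointed to the right block, and the simulation showing false survivors contained no duplicates. The repeated session-length item is a separate, smaller defect. Only the protocol article was available. A statistical analysis plan that already sets out a block comparison would meet the main point, but the nonzero-means-significant rule in the article would still need correcting.

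**What to change.** 1. For each of the four outcomes, prespecify four models on the same participants: covariates only, covariates plus time, covariates plus content, and both blocks. State whether the moderator interactions stay in the aim 3 model.
2. Report each block's unique contribution given the other, and the difference between the two with an interval. Either of these would serve for the contributions: a partial F test of each block with family-clustered errors, or out-of-fold change in R². The F tests alone do not give the difference, since one block passing and the other failing is not a contrast; the interval is needed as well. Siblings may enrol, so each family, including its bootstrap copies, must stay within one fold. Otherwise the same family sits in training and test data and R² is inflated.
3. Drop one of time features 3 and 9. Define the total, daytime and nighttime windows and the two social-AI shares, then check those sets for redundancy.
4. Stop calling a feature significant because its coefficient is nonzero; call it selected.

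Cost: no new data. Taking the both-blocks model as essentially the one already planned, there are three extra fits per outcome, 3 × 4 = 12, plus tuning repeated within each resample. The aim 2 conclusion may be less definite, particularly if analysis starts well below 1000 participants.

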Despite the highly publicized concern over the link between tech/social media use and mental health outcomes in young people, the published evidence is mixed. Many studies report associations between social media use and mental health problems [11-13], while others find weak or no relationship—or even a positive link [14-16]. One reason for these mixed findings is almost certainly that the relationship between smartphone use and mental health outcomes is not straightforward. A myriad of person-centered factors (eg, age, sex/gender identity, preexisting mental health condition, reward sensitivity), content exposure (eg, inappropriate material, cyberbullying), and nondevice activities (eg, in-person connection, physical activity) can influence the links between smartphone use and mental health outcomes [17,18].

One common feature of studies examining the mental health impacts of smartphone or social media use on young people is the nature of data collection. The literature in this area typically relies on self-reports of usage patterns by youth themselves or their caregivers [19]. However, the correlation between self-reported social media use and objectively derived use (from the devices themselves) is modest. For example, a meta-analysis of 47 studies found a correlation of 0.35 between self-reported and objectively measured social media use [20]. Given the limitations of data collection in previous studies, there is general agreement—both in the published literature and in reports from the Surgeon General and other public sources—on the need for more objective data to better understand how technology and social media use may influence mental health outcomes in young people.

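### Demographic terms share one Elastic Net penalty with the usage features, so they are shrunk and part of their effect can surface as device-use associations

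*Protocol article*

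**What the plan says.** All of this is in the protocol article, mostly under Elastic Net Regression Modeling.

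- **Role of the demographics.** "Additional features such as age, gender identity, household income, and racial and ethnic background will be included to address specific aim 3". Aim 3 is moderation.
- **How they enter.** To test moderation, "these additional features and their interaction terms will be included as independent variables in the Elastic Net model during fitting".
- **Penalty.** The only strength parameter described is "the regularization strength (λ), which scales the overall penalty". No variable-specific weight or exemption is mentioned.
- **Tuning.** "The optimal hyperparameters will be selected based on the mean squared error performance across the 10 validation folds". The criterion is prediction error.
- **What is read off.** The model is refitted on all data, and "The resulting model will provide coefficient estimates for each of the 21 device usage features and other moderating features". Nonzero coefficients are treated as significant, and moderators are followed up by comparing models with and without them.
- **Expected relations.** The Introduction names age and sex/gender identity among the factors that "can influence the links between smartphone use and mental health outcomes". The first objective under Additional Possible Analytic Approaches asks whether use patterns differ by age, sex/gender identity and race/ethnicity.

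**The concern.** A penalised fit does not adjust fully for a covariate that is itself penalised. The penalty pulls the age coefficient towards zero, and usage features correlated with age can take up some of what was removed. λ is tuned for prediction, so nothing in the procedure protects the adjustment.

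The sample spans ages 8 to 17, and the protocol itself asks whether use differs by age. A usage feature could therefore have a nonzero coefficient partly because it stands in for age, and the plan would call it significant. Aims 1 and 2 are read from these usage coefficients. As specified, they are neither unadjusted nor fully adjusted for demographics, which makes them hard to interpret even as plain associations.

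**Working it through.** **1. The plan's own figure.** Sample Size gives n=160 for 80% power with 21 predictors and f²=0.15. For the overall F test with u=21, v=160−22=138, noncentrality 0.15×160=24 and two-sided-equivalent α=0.05 (assumed, as it is not stated), power is 80.2%. With f²=0.13/0.87, power is 80.0%. The figure reproduces. It does not depend on how the demographics are penalised, so this point leaves it unchanged.

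**2. Simulation set-up.** From the documents: 21 usage features, 10-fold cross-validation on mean squared error, a mixing parameter on a grid, n=160 and n=1000. Assumed, because the documents give no values: the true coefficient of age on outcome (b), the age–usage correlation (ρ), correlated usage features with **no true effect**, and four demographic columns of which only age matters. The mixing grid was reduced to 0.1, 0.5 and 1. There were 200 replicates per setting, or 100 with interactions. Two fits were compared: one shared penalty, and demographics exempt.

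**3. Results for b=0.3.** Each cell shows shared penalty → exempt.

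| n | ρ | Age coefficient (true 0.30) | Sum of usage coefficients (true 0) | Null usage features nonzero |
|---|---|---|---|---|
| 160 | 0.3 | 0.179 → 0.296 | +0.029 → −0.007 | 17% → 10% |
| 160 | 0.5 | 0.161 → 0.298 | +0.066 → −0.008 | 20% → 10% |
| 1000 | 0.3 | 0.249 → 0.296 | +0.012 → −0.003 | 12% → 6% |
| 1000 | 0.5 | 0.243 → 0.297 | +0.026 → −0.003 | 14% → 7% |
| 160 | 0 | 0.186 → 0.294 | −0.007 → −0.006 | 17% → 10% |
| 1000 | 0 | 0.251 → 0.295 | −0.002 → −0.003 | 11% → 6% |

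Monte Carlo standard errors of the sums are about 0.005 to 0.007 at n=160 and 0.001 to 0.002 at n=1000.

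**4. Shrinkage of age (ρ=0.3 and 0.5).**
- n=160: 1−0.179/0.30=40% and 1−0.161/0.30=46%.
- n=1000: 1−0.249/0.30=17% and 1−0.243/0.30=19%.

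**5. Leakage as a share of the unadjusted signal.** With no demographics in the model, the usage coefficients sum to 0.0969 and 0.1778 (n=160) and 0.1417 and 0.2213 (n=1000).
- n=160: 0.0289/0.0969=30% and 0.0655/0.1778=37% remain under the shared penalty.
- n=1000: 0.0122/0.1417=9% and 0.0255/0.2213=12% remain.

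**6. Sensitivity.**
- With ρ=b=0.1, the sums are +0.004 (SE 0.005) at n=160 and +0.002 (SE 0.002) at n=1000, indistinguishable from zero.
- With all interactions in the model, as the plan intends (ρ=0.3, b=0.3), the sums are +0.021 at n=160 and +0.009 at n=1000. Exempting the main effects brings them to −0.009 and −0.003.

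**7. How much of the false selection is confounding?** The rows with ρ=0 are the control, since no confounding is possible there. The shared penalty still gives 17% against 10% and 11% against 6%. Counting runs with at least one falsely selected usage feature, further simulations with age as the only demographic and an age–outcome association of 0.3 gave 72–81% under the shared penalty when age and use were uncorrelated, and 77–81% at a correlation of 0.4. With age partialled out the figure was 34–43%. Most of the gap is therefore present without confounding: cross-validation picks a smaller λ so that age can be fitted, and that lets more null features through.

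**8. Time against content features.** With only the 11 time features tied to age, at 0.4, the mean numbers falsely selected were 1.6 time and 1.7 content (n=160), and 1.4 and 1.3 (n=1000). A tilt towards time features appeared only at a correlation of 0.6.

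**The case against.** **The variables are offered as moderators, and the aims speak of associations.** This is true: no adjusted or causal effect is claimed, and the Introduction sentence quoted above describes moderation, not confounding. The label does not change the fit, though. The usage coefficients are conditional on whatever demographic adjustment survives shrinkage. The planned comparison with and without the moderators sets an under-adjusted model beside an unadjusted one, so it reveals some demographic dependence but does not remove it.

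**A common penalty is inferred.** It follows from one λ and the absence of any exemption; the text does not say it outright. An analysis plan that is not shown may set penalty weights. This is the plain reading of the article, but it is a reading.

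**The leakage is small at the enrolment target.** This stands for n=1000. However, the protocol treats 160 as sufficient, and by 20 May 2025 only 106 participants had given baseline data, with 203 more in verification.

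**Stronger readings are not supported.** A reader might infer that usage features are falsely selected mainly because they proxy for age or income. The zero-correlation control shows that most of the excess arises without confounding. A reader might also infer that Aim 2 is biased towards time-on-device features. That was not seen at a correlation of 0.4, and the documents do not say that time features follow age more closely than content features do.

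**Conclusion.** The point holds in a limited form and is worth correcting before analysis. As the article is written, demographic terms are penalised together with the usage features, so their coefficients are shrunk, and part of their effect **can** appear on usage features that are then called significant. How much appears depends on correlations the documents do not give. For age–outcome 0.3 and age–use 0.3 to 0.5, about 30–37% of the unadjusted signal stays on usage features at n=160 and 9–12% at n=1000; it is negligible when both associations are about 0.1.

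Separately, the shared penalty roughly doubles the share of runs with a false usage finding. That is a product of λ selection combined with the nonzero-equals-significant rule, and should not be described as confounding.

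**What to change.** In the Elastic Net Regression Modeling text, state that the main effects of age, gender identity, household income and race/ethnicity are not penalised (penalty factor 0), or that outcome and usage features are residualised on them within each cross-validation fold. Penalise only the usage features and the interactions. If the common penalty is kept, state that the usage coefficients are predictive and not adjusted for demographics.

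The cost is one software option or one sentence, with no new data, plus a few unpenalised degrees of freedom. In the simulations the exemption brought the leakage to about zero and restored the age coefficient to about 0.30. It does not cure the significance rule: 34–43% of null runs still selected at least one usage feature, and that needs its own correction.

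### Features are declared significant from an Elastic Net tuned on a single 10-fold partition, so the list for Aims 1 to 3 can change with the fold assignment alone

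*Protocol article*

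**What the plan says.** The chain is set out in the Elastic Net Regression Modeling section of the protocol article.

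- **Resampling.** "For each outcome variable, the Elastic Net model will be trained using 10-fold cross-validation". The section then explains the scheme: "This robust method partitions the data into 10 equally sized folds", with nine folds used for fitting and one for evaluation, "repeating the process 10 times so that each fold serves as the validation set once". The ten rounds are the ten folds of one partition. They are not ten repeats of cross-validation.
- **Tuning.** The mixing parameter runs from 0 to 1 and is searched together with the penalty strength. "The optimal hyperparameters will be selected based on the mean squared error performance across the 10 validation folds".
- **Final fit.** After tuning, "the Elastic Net model will be retrained on the entire data set".
- **Decision rule.** "Variables with nonzero coefficients will be considered significant". Earlier in the same section, the nonzero coefficients of the final model identify the statistically significant predictors for Aim 1. Their pattern across outcomes informs Aim 2, and the moderators with their interactions serve Aim 3.

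The article mentions no repeated cross-validation, no averaging over partitions and no selection frequencies. It calls the method robust and says that it estimates generalization performance reliably.

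**The concern.** At the effect size the protocol assumes, the cross-validated error can be nearly flat around its minimum. Small changes in which participants share a fold can then move the chosen mixing parameter and penalty strength. Under the nonzero rule, a different penalty can mean a different set of features called significant. A reported association could thus appear or disappear with no change in the data, the outcome or the model.

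This matters most for a modest sample. The Results section reports 106 participants with baseline data at 20 May 2025 and a further 203 in verification, with first analyses planned for late autumn 2025 or winter 2026. The sample at that analysis is not stated and may be well below 1000. The data are also to be shared, so outside investigators may rerun the same procedure with a different split.

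**Working it through.** **1. Inputs from the protocol.**
- "We consider an initial set of 21 features derived from device usage within the first 2 weeks of the study": 11 time-on-device features + 6 category shares + 4 other content features = 21.
- Sample Size section: R²=0.13 (f²=0.15), 160 participants for 80% power, target 1000.
- Mixing parameter from 0 (ridge) to 1 (lasso), chosen on mean squared error over 10 folds, taken as the minimum.

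**2. Assumptions, because the article gives no figures.** Six of the 21 features are real, the penalty grid is as shown in the table, and alpha is 0.05 for the power check. In the main runs (A to F) the features form two correlated blocks of 11 and 10.

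**3. The protocol's own figure.** For the overall F test, u=21, v=160−22=138 and noncentrality f²N=0.15×160=24. The power is 0.802. With f²=0.13/0.87=0.149 it is 0.800. The stated 160 reproduces. It concerns the test that R² is zero and says nothing about which features are selected.

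**4. Simulation of the described procedure.** Each data set was held fixed and only the fold partition was redrawn. For each partition, the minimum-error settings were chosen, the model was refitted on all data, and the nonzero features were recorded. The measure is the share of pairs of partitions whose lists differ.

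| Setting | N=160 | N=1000 |
|---|---|---|
| A. 11 mixing values × 80 penalties, correlation 0.5 | 49% | 54% |
| B. As A, correlation 0.2 | – | 54% |
| C. Coarser grid, 6 mixing values × 40 penalties | 44% | 50% |
| D. As C, ridge excluded | 59% | 50% |
| E. Lasso only (N=160); R²=0.05 (N=1000) | 52% | 50% |
| F. Four moderators with interactions | 46% | 43% |
| G. Separate run, correlation 0.4, mixing 0.1 to 1 | 100−42=58% | 100−55=45% |
| H. Separate small run | 52% | 41% |

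The range is 41% to 59%. The runs used between 4 and 30 data sets each, so single percentages are imprecise.

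**5. How far two lists differ.** Where this was measured (G and H), two partitions differed on average by about 1.6 to 2 of 21 features at N=160 and by about 0.6 to 1 at N=1000. The upper ends, 2.0 and 1.1, come from G. In setting A the mean overlap (Jaccard index) was 0.81 at N=160 and 0.90 at N=1000, so at the target size most of the list is stable and mainly weak features move.

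G excludes a mixing value of 0, which the protocol allows. When a partition favors ridge, all 21 features are nonzero. In setting C this happened in 47% of partitions at N=160 and 7% at N=1000, so the averages from G leave out these jumps.

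**6. Extremes over many reruns.** Over 20 partitions in setting A, more than one list appeared in 92% of data sets at N=160 and in 100% at N=1000. About 12 and 5 features respectively changed status at least once. These counts grow with the number of reruns and do not describe a single rerun.

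**7. Does averaging help?** The table gives the number of features that changed status over the reruns.

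| Partitions averaged | N | Single partition | Averaged |
|---|---|---|---|
| 10 (6 reruns) | 160 | 4.8 | 1.2 |
| 10 (6 reruns) | 300 | 5.2 | 1.6 |
| 10 (6 reruns) | 1000 | 2.6 | 0.5 |
| 15 (8 reruns) | 300 | 5.3 | 2.0 |
| 4 | 160 | 3.5 | 2.2 |
| 4 | 1000 | 1.3 | 1.2 |

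Four partitions are too few to help much at N=1000. Ten or more help clearly.

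**The case against.** The strongest reply is that the article only explains what 10-fold cross-validation is. It does not say how folds are formed, does not forbid repeats, and may leave the seed and the number of repeats to an analysis plan that is not shown. That is fair for the seed. It does not answer the point, because the article itself fixes the sequence of tuning on ten folds, one refit, and nonzero taken as significant. As written, the reported list rests on one split.

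A second reply is that the effect is modest and the work exploratory: two partitions agree about half the time, most of the list is stable at N=1000, and selected features go on to post hoc analysis. This stands and limits the size of the point. A reader might infer that the findings cannot be reproduced from the study's own data, or that another analyst would necessarily publish a different list. The simulations do not support that, and a fixed seed gives exact repeatability.

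A reader might also infer that the protocol vouches for the stability of the selected list when it calls the method robust and reliable. In context those words concern overfitting and prediction error. No claim about selection stability is made.

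Finally, a stable list is still not a tested one. In one run at N=1000, after averaging over 15 partitions, 6.3 of the 15 features with no effect were still selected on average. Whether nonzero should mean significant is a separate and larger question, and repeated cross-validation does not settle it.

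**Conclusion.** The concern holds in a limited form. Under the procedure as described, the features reported for Aims 1 to 3 can change with the fold assignment alone. With R²=0.13, 21 features and 6 assumed real, a second partition gives a different list in roughly 40-60% of cases. The average difference is about 1.6 to 2 features at N=160 and 0.6 to 1 at N=1000. The direction was the same in every setting tried. The sizes rest on the assumed grid, correlations and number of real features, and on small simulations. This is a weakness of the primary analysis that costs little to correct. It does not by itself invalidate the aims.

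**What to change.** In the Elastic Net Regression Modeling section, replace the single partition by repeated 10-fold cross-validation, for example over 50-100 partitions. Average the cross-validated error over the repeats, choose the mixing parameter and the penalty strength once on that average, and refit once on all data.

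Report each feature's selection frequency next to its coefficient. Preferably take it from bootstrap samples or subsamples, with tuning repeated in each, because frequency over partitions of one data set shows only the noise from splitting and not sampling variability. State that the frequency measures stability and is not evidence of statistical significance.

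Fix and report the seed as well, for repeatability, but not as a substitute for the above. The cost is a few sentences and a little more computing.
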